# Swedish massage as an adjunct approach to Help suppOrt individuals Pregnant after Experiencing a prior Stillbirth (HOPES): a convergent parallel mixed-methods single-arm feasibility trial protocol

**DOI:** 10.1186/s40814-024-01499-z

**Published:** 2024-04-30

**Keywords:** Massage, Stillbirth, Mixed-methods, Termination for medical reasons, Pregnancy after loss

## Abstract

**Background:**

Women experiencing pregnancy after stillbirth experience high levels of anxiety, fear and depression. Standard antenatal care may be emotionally unsuitable for many women at this time, and there is a lack of evidence on what interventions or approaches to care might benefit these women. Therapeutic massage may assist women after stillbirth by decreasing anxiety, worry and stress.

**Objective:**

This paper outlines the objectives, methodology, outcome and assessment measures for the *Helping suppOrt individuals Pregnant after Experiencing a Stillbirth* (HOPES) feasibility trial which evaluates massage as an adjunct approach to care for pregnant women who have experienced a prior stillbirth. It also outlines data collection timing and considerations for analysing the data.

**Methods:**

HOPES will use a convergent parallel mixed-methods, single-arm repeated measures trial design in trained massage therapists’ private clinics across Australia. HOPES aims to recruit 75 individuals pregnant after a previous stillbirth. The intervention is massage therapy treatments, and participants will receive up to five massages within a 4-month period at intervals of their choosing. Primary quantitative outcomes are the feasibility and acceptability of the massage intervention. Secondary outcomes include determining the optimal timing of massage therapy delivery and the collection of measures for anxiety, worry, stress and self-management. A thematic analysis of women’s experiences undertaking the intervention will also be conducted. A narrative and joint display approach to integrate mixed-methods data is planned.

**Discussion:**

The HOPES study will determine the feasibility and preliminary evidence for massage therapy as an intervention to support women who are pregnant after a stillbirth.

Trial registration.

ClinicalTrials.gov NCT05636553. Registered on December 3, 2022, and the trial is ongoing.

## Background

There are almost 6 stillbirths a day in Australia (1, 2) where stillbirth is defined as ‘in-utero death from a 20-week gestation until immediately before birth’ (3). Stillbirth profoundly alters the reality of subsequent pregnancies (4). Pregnancy after stillbirth has been described by mothers as stress that is ‘survived’. (5) The impact of stillbirth on subsequent pregnancies is profound with mothers commonly describing conflicted emotions, high levels of anxiety and stress, fear, isolation, and a lack of trust in a good outcome (5–8). Women who have experienced a stillbirth in their previous pregnancy are at increased risk of adverse pregnancy outcomes in subsequent pregnancies such as pre-term birth and low birthweight (7, 9). The mental health of women experiencing pregnancy following stillbirth is similarly affected; with women experiencing post-traumatic stress disorder symptoms (10) and significantly more depression and anxiety than pregnant women who had not experienced a stillbirth (11, 12). Standard antenatal care is emotionally unsuitable for many women in pregnancies following a stillbirth due to their increased need of psychosocial support (13). Negative experiences of standard antenatal care include exacerbated stress and reawakened traumatic memories (5). There are few specific specialist antenatal services for women to access in a subsequent pregnancy after a stillbirth (5, 14). The international stillbirth research community has highlighted concerns about the use of traditional randomised control trial (RCT) methodologies especially when evaluating psychosocial support interventions in a pregnancy following stillbirth (15). Specific ethical concerns raised include the constraints of having a ‘treatment as usual/standard care’ intervention and withholding potentially beneficial care from those who need it (15). Methodological constraints include large sample size requirements, particularly in studies where all groups receive the active intervention (16, 17) and ‘RCT methodologies being incompatible with a much-needed individualised approach to care’ (15). Evaluation concerns in this population have contributed to the lack of direct evidence on what specific interventions or approaches to care might benefit women experiencing pregnancy after stillbirth including adjunct interventions (15). More research is needed on interventions that benefit mothers and improve their emotional health during a pregnancy after stillbirth.

Pregnancy massage aims to support the physiologic, structural and emotional well-being of both mother and fetus using various massage techniques including the Swedish and remedial massage. There is growing evidence that massage can benefit emotional health in non-pregnant and pregnant populations in various ways including by decreasing anxiety (18–25), lowering stress (20, 22, 24, 26, 27), decreasing depression (19–23, 25, 28–30) and improving mood (22, 24, 25, 31, 32). Qualitative data for massage and bereavement found massage to be helpful for recipients by generating feelings of consolidation and cultivating the feeling of support and care (33, 34). There is limited research on the aggregate effects of massage care during therapeutic alliance building, one-on-one care over time and when individualised treatments are part of the ‘treatment’ alongside massage techniques or strokes (35). A recent case study found that a patient-centred massage treatment can be a support option for women experiencing a pregnancy after stillbirth with massage assisting the ability to cope during that stressful time (36).

Massage therapy is more than the application of a massage technique and is a philosophy of care including many non-manual factors; more research encompassing massage as a philosophy of care, particularly in the antepartum population, is needed. Massage has demonstrated a precursory capacity to address the somatic and psychological symptoms associated with being pregnant after a stillbirth as well as some of the altered psycho-behavioural factors that occur in a clinical context (36). Given the precursory evidence for massage as a support option for women pregnant after stillbirth and the highlighted ethical and methodological concerns regarding withholding potentially beneficial care, treatment as usual intervention groups, sample size requirements and the need for individualised treatments for this population, a study focused specifically on the feasibility of a massage therapy intervention trial in this population is warranted before embarking on larger and more expensive effectiveness research. This paper outlines the objectives, methodology, outcome and assessment measures for the Helping suppOrt individuals Pregnant after Experiencing a Stillbirth (HOPES) feasibility trial which evaluates individualised Swedish massage as an adjunct approach to care for pregnant women who have experienced a prior stillbirth.

### Objectives

The specific objectives of the study are as follows:Assess the feasibility and acceptability of the massage intervention in the pregnant population who have a prior stillbirth experience;Determine the optimal timing of therapy, and measurement collection needs for anxiety, worry, stress and self-management;Conduct a thematic analysis of women’s experiences undertaking the intervention to evaluate the acceptability of the study processes and the intervention.

## Method

The HOPES feasibility trail began enrolment in February 2023 and expects to complete data collection in mid-2024.

The HOPES study utilizes a convergent parallel mixed-methods, single-arm repeated measures trial design aiming to assess the feasibility of Swedish massage as an adjunct approach to care for pregnant women who have previously experienced stillbirth. The convergent parallel mixed-methods design collects and analyses quantitative and qualitative individually, then compares and relates the two data types for areas of convergence or divergence and then interprets the meaning of the combined results. The primary quantitative outcomes are the feasibility and acceptability of the massage intervention. Secondary outcomes include determining the optimal timing of massage treatments and the collection of measures for anxiety, worry, stress and self-management. A thematic analysis of women’s experiences from a subsample of participants undertaking the intervention will also be conducted. The study intervention consists of up to five 60-min pregnancy massage treatments over a 4-month period at individualized time intervals per participant’s choice or availability. Each participant will complete outcome measures pre- and post-study intervention. Participants will complete a short outcome measure each pre- and post-massage treatment. A narrative and joint display approach to integrate mixed-methods data is planned.

### Study design

The study is a convergent parallel mixed-methods, single-arm repeated measures pilot trial design.

### Ethics approval and consent to participate

Human ethics approval for the study was granted by the Ethics Committee of Western Sydney University (No: H15261). Changes in protocol will undergo ethical approval. All study participants will receive written information about the study with the option for information to be provided orally. All study participants will give informed written consent for the use of their data and the application of the intervention. Participation in the study is voluntary and can be refused.

Data are treated confidentially and processed pseudonymously. The collection and storage of personal data take place in accordance with the University’s Research Data Management Policy. Shared information collected from the participants is non-identifiable using a study identifier (number). Quantitative data collected will be available for use in any other research projects in the future. To make reuse of the quantitative data possible, it will be stored under Western Sydney University’s Open Access Policy.

### Recruitment and screening

Potential participants are recruited via social media and from maternity clinics, shared care General Practitioners and obstetrician clinics around the massage therapists’ locations within Australia. Maternity services and clinics approached are based on the proximity of services to the locations of the massage therapists participating in the study. Potential participants are informed about the study via their obstetric healthcare provider or via social media platforms for stillbirth support services such as SANDS (37) and Red Nose (38). Potential participants contact the researchers via the shared contact information who explain the study and screen potential participants for eligibility (see 2.4.1 and Table 1). Potential participants are given a clear explanation of the requirements of the study, the opportunity to ask questions and time to consider their participation. Individuals who agree to take part must sign an informed consent form. Consenting individuals meeting the criteria of the study are then enrolled in the study.

**Table 1 Tab1:** Inclusion and exclusion criteria

Inclusion criteria
● Pregnant individuals 18 years of age or greater who have experienced a stillbirth or termination for medical reasons (TFMR) from 20 weeks of gestation in a previous pregnancy
● Participants must be less than 30 weeks of gestation
● Participants must be able to attend intervention visits at one of the study pregnancy massage therapists’ clinics located within Australia
● Be able to complete the intervention visits within in a 4-month period
Non-inclusion criteria
● Potential participants will be excluded if their schedule will not allow them to receive the study treatments in the allocated time frame

### Eligibility criteria

A purposeful sample of pregnant women are being recruited for the HOPES study who have experienced a stillbirth or termination for medical reasons (TFMR) after 20 weeks of gestation in a previous pregnancy (see Table 1). To be eligible to participate, pregnant women need to be less than 30 weeks of gestation. There are no criteria for eligibility related to the interpregnancy interval between the stillbirth and the current pregnancy because evidence shows the impact of stillbirth can be felt for years, and sometimes decades, after the loss (8, 39–41). The mental health of participants experiencing pregnancy after a stillbirth is varied, and we chose not to limit access to the study based on only one or two of the many mental health symptom participants may experience (e.g., anxiety, stress); especially as the mental health of participants is expected to be impacted at different time points during the pregnancy and be unique to each individual and situation (39).

### Sample size

The study aims to recruit a total of 75 pregnant people meeting the study criteria. This feasibility study is not expecting large effect sizes as anxiety and depression experienced during a pregnancy after stillbirth do not decrease until 6 months post birth (42). Thus, it is hypothesized that while the immediate effects of the massage intervention might be larger, the long-term effects will likely be small (< 0.1). Using the approach by Whitehead et al. for small effect sizes (43), it is estimated a minimum of 50 pregnant people is needed to reliably detect a small effect size (< 0.1). A sample of 75 pregnant women allows for a 10–15% drop out rate and 10% for whom data is incomplete.

A sub-group sample of 20 participants will be invited via purposive sampling to participate in the qualitative phase of the mixed-methods design. Twenty participants have been proposed as optimal to ‘improve open and frank exchange of information and mitigate some of the bias and validity concerns inherent in qualitative research’ (44). Purposive sampling will consider the type of loss (stillbirth and TFMR), early stillbirth/TMFR loss (losses between 20 and 29 + 6 weeks of gestation) and late stillbirth/TMFR loss (losses between 30 and birth).

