## Data analysis

### Analysis of quantitative data

The participant’s demographic and clinical characteristics will be summarised using descriptive statistics. Summary statistics of the observational clinical treatment data (e.g. worry, anxiety, etc.) will be reported and an appropriate matched test will be used to determine significant differences between baseline and post-final treatment scores (e.g. paired *t*-test if data are normally distributed, Wilcoxon matched-pairs test if not).

Three treatment effect modifiers have been identified: (1) the amount of other support services utilised, (2) passing the gestational age during the study intervention that they experienced their stillbirth, (3) the time between the stillbirth and this pregnancy, and (4) the number of study intervention treatments received. The correlational analysis will be used to determine associations between observational treatment outcomes and support services utilized (e.g. talk therapy (psychology/counselling), peer support etc.). Appropriate comparative tests will be used to determine whether there is a relationship between observed treatment outcomes and gestation of stillbirth, the duration of the interpregnancy interval, and the number of treatments administered.

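### The sample-size section says 50 participants can reliably detect an effect below 0.1, but the planned paired test has at most about 11% power at that size under conventional assumptions

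*Protocol article*

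**What the plan says.** The Sample size section of the protocol article sets a target of 75. It expects that "the long-term effects will likely be small", with a bound of 0.1, and then says that "it is estimated a minimum of 50 pregnant people is needed to reliably detect a small effect size", again with the bound of 0.1 in brackets. The figure of 50 is credited to a cited approach for small effect sizes. The 75 is described as allowing for 10–15% drop-out and a further 10% with incomplete data. The section gives no alpha, power, standard deviation or effect metric.

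The Study design section describes a single-arm, repeated-measures trial, so there is no comparator. For worry, anxiety and the other outcome scores, Analysis of quantitative data says that "an appropriate matched test will be used to determine significant differences between baseline and post-final treatment scores": a paired t-test if the data are normal, a Wilcoxon matched-pairs test if not. The Method section makes feasibility and acceptability the primary quantitative outcomes and the symptom and self-management measures secondary.

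**The concern.** An effect of 0.1 is far below what about 50 pairs can usually separate from zero, so the claim needed checking against the test that the protocol plans. It is the only quantitative rationale given for the sample, and it attaches to comparisons that will be reported as significant or not.

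What is at stake is how the secondary outcomes are read. Someone who takes the sentence at its word would treat a non-significant change in anxiety, worry, stress or self-management as evidence against a small effect. If the test has little chance of finding such an effect, that inference fails.

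**Working it through.** **Inputs from the protocol.** Minimum n = 50; effect below 0.1, so 0.1 is the most favourable value; target 75; losses 10–15% plus 10%; single arm; paired t-test or Wilcoxon.

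**Assumptions.** Two-sided alpha 0.05, and 0.1 as mean change divided by the SD of change (d). Neither is stated; alternatives are tried below.

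**Trying to reproduce 50.** The normal approximation is n = ((z₀.₉₇₅ + z₀.₈₀)/d)² = ((1.960 + 0.842)/0.1)², about 785. The exact noncentral-t answer is 787 pairs for 80% power and 1,053 for 90%. One-sided at 5%, the figures are 620 and 858. None is near 50. Working backwards, 80% power at n = 50 and d = 0.1 would need a one-sided alpha of 1 − Φ(0.1·√50 − 0.842) = 1 − Φ(−0.134), about 0.55.

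**Power of the planned test.** Power = P(|T| > t₀.₉₇₅,ₙ₋₁), where T is noncentral t with n − 1 degrees of freedom and noncentrality d·√n.

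| n | noncentrality at d = 0.1 | power at d = 0.1 | change detectable with 80% power |
|---|---|---|---|
| 50 | 0.707 | 10.7% | 0.40 SD |
| 57 | 0.755 | 11.5% | 0.38 SD |
| 75 | 0.866 | 13.7% | 0.33 SD |

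The plan says below 0.1, so these powers are upper bounds on this reading. At d = 0.05 and n = 50, power is 6.4%.

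**Other test settings at n = 50, d = 0.1.** One-sided 5%: 17.2%. Two-sided 10%: 18.1%. Wilcoxon, by an asymptotic relative efficiency of 0.955: about 10.3%.

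**If 0.1 is on the raw-score SD.** With pre-post correlation r, d becomes 0.1/√(2(1 − r)). The correlations are assumed.

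| r | d on change scale | power at n = 50 | pairs for 80% power |
|---|---|---|---|
| 0.3 | 0.085 | 9.0% | 1,101 |
| 0.5 | 0.100 | 10.7% | 787 |
| 0.8 | 0.158 | 19.5% | 316 |
| 0.9 | 0.224 | 34.1% | 159 |
| 0.95 | 0.316 | 59.2% | 81 |

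Power at n = 50 reaches 80% only at a correlation near 0.97.

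**Size of a significant result.** With 50 pairs, the paired t-test is significant only if the observed change is at least t₀.₉₇₅,₄₉/√50 = 2.010/7.071 = 0.28 SD, nearly three times 0.1.

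**What the sample does give.** Evaluable pairs: 75 × (1 − 0.15 − 0.10) = 56.25 at the low end and 75 × 0.90 × 0.90 = 60.75 at the high end, so about 56 to 61. This exceeds 50, so the loss allowance is not the problem. The 95% CI half-width for a mean change is t/√n: 2.004/√56 = 0.27 SD and 2.000/√61 = 0.26 SD. The change detectable with 80% power is about 0.38 SD at 56 and 0.36 SD at 61. For a feasibility proportion of 60/75 = 80%, the Wilson 95% interval is 69.6% to 87.5%.

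**The case against.** **The 50 may come from a pilot-sizing rule.** It rests on a cited approach whose inputs are not given, and that approach may not aim at detection at all. The document cannot settle this. If it is so, the number may be sound for its own purpose and the fault lies in the wording. This stands as a limit on the point: no miscalculation is shown, only that the property claimed for 50 does not hold.

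**The settings are not stated.** This also stands. The 11% is conditional on a two-sided 5% level and a standardised mean change. No conventional choice rescues the claim, however, and a correlation near 0.97 is implausible for symptom scores up to four months apart in a group whose mental health the Eligibility criteria section expects to vary over the pregnancy.

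**Feasibility is the primary aim.** True, and it limits the reach of the error. A reader might infer that the decision on a larger trial will be misled. The documents do not support this: the Feasibility success criteria rest on recruitment, retention, feeling supported and a qualitative judgement of delivery, and none uses a pre-post p-value or effect size. Nor does the point show that 75 is too few for the primary aims.

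**Two further readings go too far.** The matched test is not the only quantitative comparison, since the same section plans correlational and comparative analyses with support services used, gestation of the loss, interpregnancy interval and number of treatments. And long-term need not mean after the last assessment. The Sample size section contrasts it with the immediate effects of massage, and the Method section has measures around each massage and around the whole intervention, so it can mean change across the intervention.

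**Conclusion.** The detection claim is wrong as written. For an effect of at most 0.1, the planned paired test has at most about 11% power with 50 participants and 14% with all 75, against about 787 pairs needed for 80%. The change that 50 pairs can detect with 80% power is about 0.40 SD, four times the stated bound. These figures assume a two-sided 5% level and a standardised mean change. On the raw-score SD scale, power at 50 runs from about 9% to 59% for correlations of 0.3 to 0.95, still short of 80%.

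The consequence is confined to the sample-size rationale and the interpretation of the secondary outcome comparisons. If a true change of 0.1 SD existed, the test at n = 50 would miss it about 89% of the time (100% − 10.7%), so a non-significant result says little about a small effect. This should be fixed, but it is not critical: neither the recruitment target nor any progression rule depends on it.

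**What to change.** In Sample size, delete the claim that 50 participants reliably detect an effect below 0.1. Put in its place what the sample provides:

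- 56 to 61 evaluable pairs give a 95% CI half-width of about 0.26 to 0.27 SD for a mean change, and 80% power only for changes of about 0.36 to 0.38 SD (0.40 SD at 50 pairs), at a stated two-sided 5% level.
- 75 enrolled give a 95% CI of about 70% to 87% around a feasibility proportion of 80%.

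In Analysis of quantitative data, label the pre-post matched tests exploratory, report each change with its confidence interval, and say that a non-significant change is not evidence that a small effect is absent.

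The cost is a rewritten rationale and a change in the status of the pre-post tests. The tests can still be run, the target of 75 is unchanged, and no extra participants or data are needed. The stated capability becomes less favourable.

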### Intervention

Each participant will have access to up to 5 allocated 60-min massage consultations see Fig. 1. The massage treatments will be administered within a 4-month period at intervals of participant and therapist dyad determining based on participant preference and therapist treatment planning. Each massage consultation will be individualised to meet the needs of the participant on the day of treatment. The conceptual approach utilized is based on a vulnerability-to-stress concept. The vulnerability-to-stress concept acknowledges the impact of stress on vulnerability and recognises protective factors that can help reduce stress (45). For women pregnant after a stillbirth, the vulnerability is the previous loss (and any other pregnancy losses) as well as any biological factors, and the stress is being pregnant again (and the fear of another loss). We are proposing that massage might be a protective factor to help manage stress. This conceptual approach was used in a published case study (36). The massage aims to support women by addressing altered psycho-behavioural and physiological factors associated with vulnerability and stress such as countering feelings of loss of control via allowing participants to individualise their treatments (e.g. depth, area of the body to be treated, what they want to be treated). See Additional file 1 for the protocol for the massage which covers more in-depth how massage may do this. The massage intervention uses hands-on techniques, listening and creating the environment to build a therapeutic alliance to help provide protective factors and manage the stress of pregnancy after a stillbirth. Allowable massage strokes for therapist incorporation into treatment to address the study aims include longitudinal gliding, transverse gliding, digital ischemic pressure, transverse frictions and transverse gliding. The use of these massage strokes is based on prior pregnancy massage research (39, 42). The areas of the body treated, the depth of treatment and which massage strokes used will be determined by the massage therapist reflecting real-world clinical massage practice. No other form of massage therapy or hands-on modalities (e.g. reflexology, aromatherapy massage) are to be used and nor are other healing modalities (e.g. reiki). Treatment sessions are 60 min and include hands-on treatment time as well as the time prior and after the hands-on massage to consult with the participant about their treatment and plan the timing for the next treatment session. See Additional file 1.
